## Abstract

**Background:** Given the complexity of stroke treatment and the current widespread use of traditional Chinese medicine (TCM) in the absence of robust, large, long-term effectiveness and safety studies, and the lack of nationwide epidemiology and clinical characteristics of patients with stroke receiving TCM treatment, the acquisition of data from longitudinal cohorts is essential. We intend to generate the major clinical characteristics of patients with stroke who receive TCM treatment and to investigate the effectiveness and safety of TCM in the Chinese population.

**Methods:** The China Stroke Registry for Patients with Traditional Chinese Medicine (CASES-TCM) study is a prospective, multicenter, observational disease registry aiming to register 20,000 hospitalized patients. Eligible adult patients with clearly diagnosed acute ischemic stroke or intracerebral hemorrhage within 7 days of symptom onset will be consecutively registered from 126 participating sites across China. Baseline data will be recorded, and all patients will be regularly followed up at 3, 6, 12, and 24 months after stroke onset. Collected data will be entered into a web-based system with high-level data security. The primary outcomes include the distribution of scores on the modified Rankin Scale at the 3-months follow-up, and recurrent stroke events within the 12-months follow-up.

**Conclusion:** To our knowledge, the CASES-TCM study is the first and largest nationwide registry to document comprehensive data on TCM treatment in patients with acute stroke. The findings of this study will be valuable to improve our knowledge about TCM treatment for patients with stroke and its subsequent outcomes in the actual clinical setting, consequently facilitating and standardizing the optimization of individualized interventions with TCM for stroke prevention and treatment in China.

**Study registration:** This study was registered with Clinicaltrials.gov (URL: https://clinicaltrials.gov/, Unique identifier: NCT04921397).

## Introduction

Stroke is the second leading cause of death globally, and it ranks first in China, in which the annual stroke mortality rate is approximately 114.8/100,000, which is five times that of American and European countries (Wang et al., 2017; GBD 2019 Diseases and Injuries Collaborators, 2020; Zhou et al., 2019). Stroke poses a heavy health and economic burden, which is expected to increase further as a result of population aging (Rajsic et al., 2019). The distribution of stroke burden varies among different regions in China (Wang et al., 2017). Ischemic stroke and intracerebral hemorrhage (ICH) are the two most common subtypes of stroke with a total proportion of roughly 90% (Wang et al., 2011).

The current status of stroke treatment remains unoptimistic, although substantial progress has been achieved. Reperfusion therapy has been recommended as the first-line treatment of acute ischemic stroke (AIS) for improving long-term functional outcome, but it only benefits a limited number of patients given the narrow time-window, imaging dependence, high technical requirements, advanced catheter systems, and requirement for extensive economic resources (Powers et al., 2015; Powers et al., 2019). Although antiplatelet, lipid-lowering, and antihypertensive therapy carry remarkable effects for the secondary prevention of stoke (Wang et al., 2016a), more than half of the Chinese population bear aspirin or clopidogrel resistance (Wang et al., 2016b; Yi et al., 2016), and poor long-term medication compliance merits attention (Wei et al., 2010; Chen et al., 2014). As for ICH, there are no specific treatment options for patients who are ineligible for surgery (Hemphill et al., 2015). Consequently, traditional Chinese medicine (TCM) therapy, as an important, and alternative approach to the treatment of stroke, warrants investigation.

TCM has been applied in stroke treatment for thousands of years in China (Chan, 2014). TCM is popularized with wide acceptability, and results of the China Quality Evaluation of Stroke Care and Treatment study, which examined the clinical practice and secondary prevention of stroke in China, indicated that TCM accounted for 83.1% of AIS medication treatment and 42% of ICH treatment (Group of the China Quality Evaluation of Stroke Care and Treatment, 2009; Wei et al., 2011). Additionally, deemed as a part of TCM, acupuncture for stroke treatment has been used in China for over 1,000 years and is increasingly practiced in some western countries (Wu et al., 2006; Zhang et al., 2015).

However, the epidemiology and clinical characteristics of patients with stroke receiving TCM treatment remain unknown, and the actual effects concerning benefits and harms of TCM for stroke are still conflictive. Some of the therapeutic effects of TCM on stroke treatment have been proven by previous clinical trials in terms of alleviating neurological impairment (Gao L et al., 2012), improving long-term physical disability and handicap (Hu et al., 2020), facilitating limb, language and dysphagia recovery (Liu and Zhang, 2006; Zhang et al., 2013; Xia et al., 2016; Yu et al., 2021), accelerating hematoma absorption (Gao Y et al., 2012; Li et al., 2016), and reducing recurrent stroke events (Chen et al., 2013a; Cai et al., 2019). These trials were conducted at ideal conditions without multiple confounding factors, indicating that external application of TCM treatment requires validation under updated clinical practice. Moreover, no evidence of comparative effectiveness is available from cohorts of patients treated outside the context of clinical trials. By contrast, several trials demonstrated that TCM neither improved long-term functional outcome of AIS nor reduced hematoma enlargement in ICH (Chen et al., 2013b; Zeng et al., 2019). The possible reasons may lie in similar reflection on the failure of past trials, which includes wrong timing or wrong dosage of TCM administration, inadequate sample size, inaccurate target population, and inter-center variations in treatment (Deans et al., 2007; Vincent, 2010; Macdonald et al., 2013). Additionally, as one of the largest cohort studies regarding acute cerebrovascular events in previous decades in China, the China National Stroke Registry (CNSR) demonstrated that the wide usage of TCM treatment might be associated with higher stroke recurrence (Qin et al., 2021). However, it is notable that the CNSR did not report detailed TCM treatment information but only roughly recorded TCM as an exposure.

Considering the importance of clinical data on stroke in the Chinese population treated with TCM in the real world, and to help fill the clinical gap, we therefore designed the China Stroke Registry for Patients with Traditional Chinese Medicine (CASES-TCM) study to generate sociodemographic and medical data relating to patients with stroke receiving TCM treatment and to investigate the effectiveness and safety of TCM for stroke in the Chinese population.

## Methods and Design

### Study Design

The CASES-TCM study (registered with ClinicalTrials.gov, Unique identifier: NCT04921397) is a prospective, multicenter, observational disease registry, attempting to depict major clinical characteristics of stroke in patients treated with TCM and to explore any difference in the comparison with other non-TCM user cohorts and the effectiveness and safety of TCM. An overview of this study flowchart is shown in Figure 1. The registry protocol was approved by the institutional review board of the leading center, Dongzhimen Hospital, Beijing University of Chinese Medicine, Beijing, China (No. 2021DZMEC-024-02), and will be approved by the local institutional review boards of all participating sites.

**FIGURE 1 F1:**
[figure not shown]
The flowchart of the CASES-TCM study; Abbreviations: AIS, acute ischemic stroke; ICH, intracerebral hemorrhage; TCM, traditional Chinese medicine.

### Patient Population

Adult patients (≥18 years) admitted to Chinese hospitals with AIS or ICH diagnosed according to the corresponding guidelines, respectively, are eligible for inclusion in the CASES-TCM study (Hemphill et al., 2015; Powers et al., 2019). Only patients within 7 days of symptom onset will be included. Patients who have difficulties with follow-up completion will be excluded. Written informed consent including participation, data collection, and publication will be obtained from all patients or their legally authorized representatives in this study. Patient participation will be entirely voluntary, and patient’s data will be strictly protected. There is no specific risk of participation in this study. Instead, patients will receive regular medical guidance from doctors during the follow-up period. Patient registry is expected to begin in September 2021.

### Specific Treatment

Different kinds of TCM treatment for patients with stroke will be included because we will focus on whether doctors use TCM based on individual syndrome differentiation, which is etiology in view of TCM theory. We will record TCM application settings including prehospital stage (at home or ambulance), in-hospital stage (emergency department or neurology ward), and hospital discharge (community or at home), and TCM formulations including Chinese patent medicine (injection or oral agents), and TCM compounds. The initiation time of TCM administration for patients with stroke and adherence to TCM treatment will also be recorded. As for other routine treatments, doctors will treat patients with stroke according to the corresponding Chinese guidelines (Chinese Society of Neurology, 2018; Chinese Society of Neurology, 2019). The common management methods include basic control of risk factors, intravenous thrombolysis, mechanical thrombectomy, antiplatelets, anticoagulants, and neuroprotective agents. Additionally, doctors will determine the treatment strategies based on their clinical experience and the patients’ condition when no guideline-recommended therapies are applicable.

### Main Variables

We established the minimum dataset that includes the main variables using a stepwise approach. To ensure the balance between feasibility and scientificity, we pooled the variables from our previous studies (ChiCTR1800016363, NCT02728180, ChiCTR-OPC-16008451, ChiCTR1900026422) on stroke survey and treatment, which were funded by the Stroke Prevention Project Committee National Health and Family Planning Commission, and the Ministry of Science and Technology of the People’s Republic of China. Taking into account the TCM treatment features, patient burden, potential loss to follow-up, and comparability to variables of other representative large-scale registry studies, we adjusted the variables and finally determined the minimum dataset *via* expert consensus. The expert panel consisted of clinicians, researchers, healthcare nurses, and experts from other disease registries. Table 1 lists the main variables that will be collected during the study.

**TABLE 1 T1:** Main variables registered in CASES-TCM study.

Field	Variables
**Basic Information**	
Demographic	Age; Gender; Ethnicity; Education; Birthplace; Permanent address; Height; Weight; Body Mass Index; Marital status; Pregnancy; Occupation; Medical insurance
**Baseline Information (At admission)**	
Symptom onset	Symptom onset date; Solar terms; Five evolutive phases and six climatic factors (*Wuyun Liuqi*); Admission date; Pre-onset transient symptoms; Pre-onset mRS; Condition at onset; Initial symptoms
Admission evaluation	NIHSS; GCS; mRS; BI; MMSE; DSSEIS
Past medical history	Cerebrovascular diseases; Heart diseases; Hypertension; Diabetes mellitus; Dyslipidemia; Peripheral arterial disease; Hyperuricemia; Hyperhomocysteinemia; Others
Personal history	Smoking; Alcohol consumption; Lifestyle (diet preference; exercise frequency)
Pre-hospital care and treatment/Previous medication	First aid transport mode; Reperfusion therapies (IVT; EVT) for AIS; Surgery for ICH; Antiplatelet agents; Anticoagulants; Neuroprotective agents; TCM (specific medicine; acupuncture; application setting), Others
Auxiliary examination	Vital signs; Laboratory tests completed within 24 h; ECG; Neuroimaging; Examination for other risk factors
Primary diagnosis	AIS or ICH; Chinese Medicine Diagnosis; OCSP classification of AIS/Lesion classification of ICH
**Discharge Information**	
Auxiliary examination	Vital signs; Laboratory tests
Final diagnosis	TOAST classification of AIS; SMASH-U classification of ICH; In-hospital complications
In-hospital treatment	Reperfusion therapies (IVT; EVT) for AIS; Surgery for ICH; Antiplatelet agents; Anticoagulants; Lipid-lowering agents; Antihypertensive agents; Hypoglycemic agents; Neuroprotective agents; TCM (Chinese patent medicine; TCM compounds; acupuncture; others): including administration time and dose
Discharge evaluation	NIHSS; GCS; mRS; BI; MMSE; DSSEIS; PRO-Stroke
**Follow-up Information**	
Major events	Death; New cardiovascular events; New cerebrovascular events; Adverse events
Adherence to secondary prevention	Antiplatelet agents; Anticoagulants; Lipid-lowering agents; Antihypertensive agents; Hypoglycemic agents
Adherence to TCM treatment	Specific medicine; Proportion of days covered of TCM treatment
Follow-up evaluation	mRS; BI; MMSE

mRS, modified Rankin Scale; NIHSS, National Institutes of Health Stroke Scale; BI, Barthel Index; MMSE, Mini-Mental State Examination; DSSEIS, Diagnostic Scale of Syndrome Elements in Ischemic Stroke; IVT, Intravenous thrombolytic therapy; EVT, endovascular treatment; AIS, acute ischemic stroke; ICH, intracerebral hemorrhage; TCM, traditional Chinese medicine; ECG, electrocardiogram; OCSP, Oxfordshire Community Stroke Project; TOAST, Trial of Org 10172 in Acute Stroke Treatment; SMASH-U, Structural lesion, Medication, Amyloid angiopathy, Systemic/other disease, Hypertension, Undetermined; PRO-Stroke, Patient-Reported Outcome Scale for Stroke.

### Data Collection and Monitoring

During patient admission, trained research personnel who are appointed at each participating site will collect baseline data regarding prehospital care and treatment, pre-stroke symptom, and the pre-stroke modified Rankin Scale (mRS) score and will perform assessments using the Glasgow Coma Scale (GCS), National Institute of Health Stroke Scale (NIHSS), Barthel Index (BI), Mini-Mental State Examination (MMSE), and Diagnostic Scale of Syndrome Elements in Ischemic Stroke (DSSEIS). The patients’ demographics, medical history, family history, physical examination, auxiliary examination, risk factor assessment, and clinical diagnosis will be extracted from medical records. Research personnel will perform GCS, NIHSS, mRS, BI, MMSE, DSSEIS, and Patient-Reported Outcome Scale for Stroke (PRO-Stroke) assessment through a face-to-face interview during patient discharge. The etiologic classification of stroke, stroke-related complications, and new cerebrovascular events will be extracted. The etiologic classification of AIS will be determined according to the Trial of Org 10172 in Acute Stroke Treatment (TOAST) criteria while ICH according to the Structural lesion, Medication, Amyloid angiopathy, Systemic/other disease, Hypertension, Undetermined (SMASH-U) criteria (Adams et al., 1993; Meretoja et al., 2012). In addition to conventional therapies, research personnel will record the type of TCM treatment that is defined according to the World Health Organization (World Health Organization, 2011), details involving Chinese patent medicine, TCM compounds, hospital preparation of TCM, acupuncture, and moxibustion during hospitalization. Data collection and reporting will be conducted using an electronic data capture (EDC) system (http://www.1-dao.net:13579/) with a unique ID. Research personnel can also launch this EDC system on smartphones, and they will complete data collection when they are on daily ward rounds. All laboratory test and auxiliary examination results will be collected. The EDC system can remind research personnel of patients’ follow-up, and it can also automatically check for completeness, coding, value range, and logical error of uploaded data, and then provide feedback to research personnel. Any uploaded data correction, as well as electronic audit trail with electronic signature and date, will be recorded on the system. This registry system is housed on a secure server at the Institute for Brain Disorders, Beijing University of Chinese Medicine. An independent contract research organization will perform online data monitoring during the whole study.

### Follow-Up Procedures

All patients will be identified and followed up using individual identity cards that are unique to every Chinese citizen, enabling unambiguous linkages. Research personnel will regularly perform face-to-face or telephone follow-up at 3, 6, 12, and 24 months after stroke onset. Information, including death, functional status, activity of daily living, cardiovascular or cerebrovascular events, cognitive function, and adherence to secondary prevention recommendation and TCM treatments, will be obtained. Death will be confirmed *via* a death certificate from the local civil registry or from the attended hospital. New cardiovascular or cerebrovascular events leading to rehospitalization will be confirmed by the discharge diagnosis. Suspected recurrent cardiovascular or cerebrovascular events will be determined by the endpoint judgment committee if without hospitalization (Wang et al., 2019).

### Study Outcomes

In the CASES-TCM study, the distribution of scores on the mRS at the 3-months follow-up, and any recurrent stroke events including ischemic and hemorrhagic stroke (ICH and subarachnoid hemorrhage) within the 12-months follow-up will be set as the primary outcomes. Secondary outcomes, which will be assessed at different follow-up visits, include the following: exposure and adherence to TCM treatment, improvement of neurological deficits, patients’ subjective feelings, death, functional outcome, activity of daily living, cognitive function, composite of new clinical vascular events, and incidence of adverse events. The complete outcomes of the CASES-TCM study are illustrated in Table 2.

**TABLE 2 T2:** The complete outcomes of CASES-TCM study.

**Primary outcomes**
Distribution of scores on the mRS at 3-months follow-up
Recurrent stroke events (ischemic stroke, hemorrhagic stroke including intracerebral hemorrhage and subarachnoid hemorrhage) within 12-months follow-up
**Secondary outcomes**
Proportion of patients receive TCM treatment within 24 h after admission
TCM treatment duration within 3-months, 12-months, and 24-months follow-up
Change in the NIHSS score between baseline (admission) and discharge (14 days—mean for length of hospitalization for stroke patients)
Patient-Reported Outcomes Scale for Stroke score at discharge (14 days—mean for length of hospitalization for stroke patients)
Proportion of patients with mRS score ≤2 at 3-months and 12-months follow-up
Distribution of scores on the mRS at 12-months follow-up
Proportion of patients with BI score ≥90 at 3-months and 12-months follow-up
Recurrent stroke events (ischemic stroke, hemorrhagic stroke including intracerebral hemorrhage and subarachnoid hemorrhage) within 3-months and 24-months follow-up
Composite of new clinical vascular events within 3-months, 12-months, and 24-months follow-up
MMSE scale score at 3-months, 12-months, and 24-months follow-up
All-cause mortality within 12-months and 24-months follow-up
Incidence of adverse events during the whole study

mRS, modified Rankin scale; TCM, traditional Chinese medicine; NIHSS, National Institute of Health Stroke Scale; BI, Barthel Index; MMSE, Mini-Mental State Examination.

### Study Sites and Data Source

The steering committee of the CASES-TCM study will screen hospitals nationwide from each region in the north, east, west, south, and center of mainland China to represent the population. Participating sites in our study are required to admit over 100 cases of patients with stroke per year, have experienced multicenter studies, and be equipped with magnetic resonance imaging or computed tomography machines. A total of 126 participating sites with qualified research capability and proven commitment to the study will be ultimately selected. Figure 2 illustrates the geographical distribution of the selected participating sites.

**FIGURE 2 F2:**
[figure not shown]
Sites distribution of CASES-TCM study.

### Quality Control and Management

Prior to study initiation, the steering committee will create training videos regarding the study protocol and standard operating procedures (SOPs) in terms of consecutive patient screening and recruitment, obtaining informed consent, and data collection. Research personnel will be required to complete the training videos and obtain a study permit once they pass the examination. The endpoint judgment committee will be responsible for developing SOPs concerning the proper use of scales, outcome assessment, and reporting procedures. An independent data safety and monitoring board will conduct data monitoring to ensure adherence to study documentation, reporting procedures, and the study protocol.

### Study Sample Size

Generally speaking, the sample size of the registry study should be sufficiently large enough to represent the general population. Based on the annual number of 20 cases of hospitalization per month due to acute stroke in every participating site (a total of 126 sites), we aim to register 20,000 patients in the CASES-TCM study. Enrolment of up to 20,000 patients is anticipated at the end of the first year.

### Statistical Analysis

A statistical analysis plan (SAP) has been developed prior to the initiation of the CASES-TCM registry. All collected observational data will be analyzed descriptively using established statistical methods. The mean, median, standard median, or interquartile ranges will be used to summarized continuous data, while counts or percentages for categorical data. Between-group comparisons will be conducted using parametric tests [one-way analysis of variance (ANOVA) or Student’s t-test] or non-parametric tests (chi-square test, Fisher’s exact test, Kruskal–Wallis one-way ANOVA on ranks, or Mann–Whitney *U* test), as appropriate. As for time-to-event analysis, patients will be censored at their last follow-up assessment when experiencing a clinical event, at the end of study, or at the time of withdrawal from the study. Cumulative clinical events will be reported as Kaplan–Meier estimates. Cox proportional hazards regression methods will be used for hazard ratio calculation at 95% confidence intervals, and the treatment effect will be assessed using the log-rank test. During the analysis, confounding factors will be considered, and multivariable regressions will be conducted with adjustments for potential covariates and the propensity score. If not specified otherwise in the SAP, missing data will not be imputed. Subjects with incomplete data will be included in the analysis and for each variable; the number of subjects with missing data will be reported. Interim analyses comprising descriptive summaries of collected data will be conducted every 6 months. All statistical tests will be two-sided and statistical significance will be set at *p* < 0.05. Statistical analyses will be performed using SAS software version 9.4 (SAS Institute, Inc.).

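### The named between-group tests, and the log-rank test given the treatment effect, ignore hospital, and the article does not say that site enters the regressions or the propensity score

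*Protocol article*

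**What the plan says.** The Statistical Analysis section of the protocol article states "Between-group comparisons will be conducted using parametric tests" (ANOVA, t-test) or non-parametric ones (chi-square, Fisher, Kruskal–Wallis, Mann–Whitney). Time-to-event outcomes get Kaplan–Meier estimates and Cox hazard ratios, and the treatment effect is to be assessed by the log-rank test. On level, it says "All statistical tests will be two-sided and statistical significance will be set at" p < 0.05.

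The section also promises that confounding will be considered, through multivariable regressions adjusted for covariates it does not name and for a propensity score. It says that a SAP was written before the registry began; that SAP is not shown. The section mentions no site term, stratum, random effect, frailty or robust variance.

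On scale, Study Sites and Data Source has "A total of 126 participating sites with qualified research capability and proven commitment to the study will be ultimately selected", drawn from five regions, and Study Sample Size has "we aim to register 20,000 patients in the CASES-TCM study". The Introduction lists "inter-center variations in treatment" among the possible reasons why earlier trials failed. Study Design includes a comparison with patients who do not use TCM, and the effectiveness of TCM, among the aims.

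**The concern.** Patients treated in one hospital tend to resemble each other in outcome, and they share its habits of prescribing. If TCM use differs between hospitals, a test that treats every patient as independent can go wrong in two ways.

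- **Precision.** The standard error of the TCM comparison is too small, so the nominal 5% test rejects too often.
- **Bias.** If hospitals that use more TCM also have better or worse outcomes for other reasons, that difference is read as a TCM effect. More patients make this error look more certain and do not reduce it.

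Both primary outcomes are exposed. Recurrent stroke within 12 months is a time-to-event outcome, and the log-rank test named for the treatment effect has, as written, no site stratum. The mRS distribution at 3 months would fall under the listed between-group tests.

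Several features make differences between hospitals plausible. Treatment is left to the doctor's judgement where no guideline therapy applies (Specific Treatment). Hospital preparations of TCM are recorded (Data Collection and Monitoring). Events that lead to rehospitalisation are confirmed by the discharge diagnosis (Follow-Up Procedures).

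**Working it through.** **Inputs from the article**
- 20,000 patients (Study Sample Size) and 126 sites (Study Sites and Data Source).
- Two-sided alpha 0.05 (Statistical Analysis).
- No ICC, effect size or power is given.

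**The plan's own figure.** The stated basis is "Based on the annual number of 20 cases of hospitalization per month due to acute stroke in every participating site", and "Enrolment of up to 20,000 patients is anticipated at the end of the first year". Read as 20 per month, 126 × 20 × 12 = 30,240, which does not reproduce 20,000. This is a separate matter. I use 20,000. The larger figure would give 30,240/126 = 240 patients per site and hence a stronger clustering effect.

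**Step 1: cluster size.** m = 20,000/126 = 158.7.

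**Step 2: effect of ignoring site on the standard error.** For an exposure measured in each patient:

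DE = 1 + (m − 1) × ICC(outcome) × ICC(exposure)

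The exposure ICC is 0 when TCM use is equal across hospitals and 1 when it is fixed by hospital. The true standard error is √DE times the naive one. The actual type I error of the nominal 5% test is 2 × (1 − Φ(1.96/√DE)), and the effective sample size is 20,000/DE.

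Lower example: DE = 1 + 157.7 × 0.01 × 0.3 = 1.47; √1.47 = 1.21; 1.96/1.21 = 1.62; type I error 0.106.

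Upper example: DE = 1 + 157.7 × 0.05 × 1 = 8.89; √8.89 = 2.98; 1.96/2.98 = 0.66; type I error 0.511.

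| Outcome ICC (assumed) | Exposure ICC (assumed) | DE | SE factor | Effective n | Type I error |
|---|---|---|---|---|---|
| 0.01–0.05 | 0 | 1.00 | 1.00 | 20,000 | 0.050 |
| 0.01 | 0.3 | 1.47 | 1.21 | 13,576 | 0.106 |
| 0.02 | 0.3 | 1.95 | 1.40 | 10,275 | 0.160 |
| 0.05 | 0.3 | 3.37 | 1.83 | 5,942 | 0.285 |
| 0.01 | 1 | 2.58 | 1.61 | 7,760 | 0.222 |
| 0.02 | 1 | 4.15 | 2.04 | 4,814 | 0.336 |
| 0.05 | 1 | 8.89 | 2.98 | 2,251 | 0.511 |

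**Step 3: bias.** A simulation used 126 sites of 159 patients, a continuous outcome, no true TCM effect, outcome ICC 0.01, 0.02 and 0.05, and 400 runs per setting. The log-odds of TCM use had a between-site SD of 0, 1 or 2. Two analyses were compared at the 5% level: one ignoring site, and one using within-site contrasts only.

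| Setting | Rejection, site ignored | Spurious effect, site ignored (SD units) |
|---|---|---|
| TCM use equal across sites | 0.028–0.070 | about 0 |
| TCM use varies by site, unrelated to site outcome | 0.085–0.328 | about 0 |
| TCM use varies by site, correlation 0.3 with site outcome | 0.405–0.978 | 0.025–0.083 |

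The within-site analysis rejected in 0.030 to 0.072 of runs, with mean effect near 0, in every setting. With 400 runs the simulation error around 0.05 is about ±0.022 (2 × √(0.05 × 0.95/400)), so these rates agree with 5%. The outcome was continuous, so the simulation shows the mechanism and is not a forecast for mRS or recurrence.

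**The case against.** The strongest reply is that this is a condensed article with a SAP behind it, and that handling of site is commonly left to a SAP. The regression covariates and propensity-score variables are unnamed, so site may be among them, and naming a Cox model does not rule out strata, frailty or robust variance. This stands. A reader might infer that every planned model ignores hospital; the documents do not support that. For the regressions, all that can be said is that the article is silent.

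The premises can also be challenged. The Introduction's remark on variation between centres concerns past trials and treatment, not these 126 sites or their outcomes. TCM is described as chosen by individual syndrome differentiation and is recorded patient by patient. Routine care follows common guidelines, site staff must pass an examination, and an endpoint committee writes the outcome procedures and judges suspected events that did not lead to hospitalisation. So a reader who infers that TCM use and outcome coding are driven by hospital goes beyond the text. This stands too, although none of these features shows that clustering is absent.

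Nor should the table be read as showing that the intervals are wrong or that the error rate is 22% to 51%. Those rates need TCM use to be fixed by hospital, at ICCs the documents do not give. The only confidence intervals the section mentions are for hazard ratios, so a claim about intervals for national rates would concern output it does not specify.

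The reply does not reach what the section states positively: a list of simple tests for group comparisons, and the log-rank test for the treatment effect. Those are choices in the text. As written they have neither a site stratum nor a variance that allows for clustering.

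**Conclusion.** The point holds in a limited form. The named between-group tests and the log-rank test for the treatment effect ignore hospital, and the article does not say that the regressions or the propensity score include it. If these tests carry the TCM comparison as written, the type I error is 5% when TCM use is equal across sites, about 11% to 29% at exposure ICC 0.3, and about 22% to 51% for a fully site-level exposure, in each case for outcome ICC 0.01 to 0.05. The formula also assumes equal site sizes. Correlation between a site's TCM use and its outcomes would add bias that 20,000 patients cannot average away.

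A reader might conclude that hospital effects are confounded with TCM in this registry. The documents make that a plausible risk, not a fact: they report no variation in TCM use or outcome across the sites. Purely descriptive summaries are affected only in their precision. The point deserves action because the remedy is cheap and the comparison is a stated aim.

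**What to change.** Confirm in the SAP, or add to it, for every comparison of TCM effectiveness:

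- **Variance:** site-clustered (robust) standard errors.
- **Recurrent stroke:** base inference on a Cox model stratified by site, or a site-stratified log-rank test, in place of the unstratified log-rank test.
- **mRS distribution:** base inference on an ordinal model with a site effect. The site's proportion of TCM use may be added to separate within-hospital from between-hospital contrasts; this term is optional.
- **Propensity score and covariates:** state whether site is included.
- **Unadjusted tests:** label the t-test, ANOVA, chi-square, rank tests and unstratified log-rank as descriptive.

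The cost is SAP wording. Enrolling site is already known for each patient, and the planned software, SAS 9.4, covers these methods. No extra patients or visits are needed. The price is somewhat wider intervals, and hospitals where nearly all or nearly no patients receive TCM contribute little to a within-hospital contrast. The SAP should acknowledge that this shifts the question towards the effect of TCM within hospitals.
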